### Sample size calculation

Calculation of the required sample size is based on the assumption that the mean Constant score will be 47 in the conservatively treated patients and 56 in the HA group, assuming a SD of 12 for each group [10,14].

A two-sided test with an alpha level of 0.05 and a beta level of 0.2 requires 30 patients in every group. Anticipating a mortality rate of 10% in the first year due to a natural death rate in elderly patients [36], and a conservative dropout rate of 20% loss-to-follow up (based upon experience in previous trials), projects to a required sample size of 40 per group.

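### Forty per group leaves 28 to 29 evaluable patients, not 30, under the stated 10% mortality and 20% loss to follow-up; power stays at about 80%

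*Protocol article*

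**What the plan says.** All the figures are in the Sample size calculation section of the protocol article. It assumes "the mean Constant score will be 47 in the conservatively treated patients and 56 in the HA group", and takes the standard deviation to be 12 in both arms. From this it concludes: "A two-sided test with an alpha level of 0.05 and a beta level of 0.2 requires 30 patients in every group".

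It then names two losses. The first is death: "Anticipating a mortality rate of 10% in the first year", supported by a citation on natural mortality in the elderly. The second is "a conservative dropout rate of 20% loss-to-follow up", attributed to experience in previous trials. The section ends by saying that this "projects to a required sample size of 40 per group". The Abstract gives the matching total of 80.

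The Abstract and the Study objectives place the primary comparison of Constant scores at one year, the same horizon as the mortality figure.

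**The concern.** The 30 is the number needed before allowance for death and dropout, so it has to be read as the number with a primary outcome. To have 30 left after losing a share d, one must randomise 30/(1 - d). With the two stated rates this does not give 40.

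The sample size is therefore not reproducible from its own inputs by the correct method. Anyone who takes the section at face value will believe that 30 per arm are protected against the stated attrition when they are not. What is at stake is the accuracy of the sample size justification and, to a small degree, the power that can be claimed.

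**Working it through.** **Inputs** (all from Sample size calculation): means 47 and 56, so a difference of 9; SD 12, so a standardised difference of 9/12 = 0.75; two-sided alpha 0.05; power 80%; 30 required per group; 10% mortality; 20% loss to follow-up; 40 randomised per group. The section gives no horizon for the 20%; I take it to apply by one year.

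**Step 1: reproduce the 30.** By normal approximation, n = 2 x (1.96 + 0.8416)² x 12²/9² = 2 x 7.849 x 144/81 = 27.9, so 28 per group. The t-test calculation gives 28.9, so 29. The stated 30 is 1 to 2 above what 80% power needs, and is a reasonable rounding up.

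**Step 2: reproduce the 40.**

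| Method | Calculation | Per group |
|---|---|---|
| Multiply up, both rates | 30 x 1.10 x 1.20 = 39.6 | 40 |
| Multiply up, summed rate | 30 x 1.30 = 39.0 | 39 |
| Divide, losses in sequence | 30/(0.90 x 0.80) = 41.7 | 42 |
| Divide, losses added | 30/(1 - 0.30) = 42.9 | 43 |

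Of these, only the first gives 40. Multiplying up by the loss rate gives too few patients, because the losses then also apply to the added patients.

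**Step 3: evaluable patients out of 40.**
- Losses added: 40 x 0.70 = 28.0, a shortfall of 30 - 28.0 = 2.0 per arm.
- Losses in sequence: 40 x 0.90 x 0.80 = 28.8, a shortfall of 30 - 28.8 = 1.2 per arm.

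Check of the divided figures: 42 x 0.72 = 30.2 and 43 x 0.70 = 30.1, so both keep 30.

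**Step 4: power for a difference of 9 with SD 12.** The normal approximation is Φ(0.75 x √(n/2) - 1.96). The t-test column uses the noncentral t distribution.

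| Evaluable per group | Normal approximation | t-test |
|---|---|---|
| 28 | 80.1% | 78.7% |
| 28.8 | 81.2% | 79.9% |
| 29 | 81.5% | 80.1% |
| 30 | 82.8% | 81.5% |
| 32 | 85.1% | 84.0% |

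By t-test, the difference detectable with 80% power is 8.83 points at 30 per group, and 9.02 to 9.15 points at 28.8 to 28.0. The assumed difference is 9.

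**The case against.** The strongest defence is that 30 already contains slack. It does: the plan's inputs need 28 by normal approximation, and even with the losses added 28/0.70 = 40.0 exactly. On that basis 40 randomised patients still deliver 80% power. By t-test the base is 29, and 29/0.72 = 40.3 or 29/0.70 = 41.4, so 41 to 42 would be needed, which is hardly different. This stands as a limit on the consequence. It does not rescue the sentence, which names 30 as the requirement and presents 40 as the number that protects it.

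A second defence is that the 20% may include the deaths. Then 40 x 0.80 = 32 remain and there is no shortfall. The wording is against this, because the two rates are listed separately, each with its own justification. It would not produce 40 either: 30/0.80 = 37.5, so 38. It is still a possible intention that the text should settle.

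A reader might infer three stronger things that the document does not support:
- *That the 80% power claim fails.* The section does not say how the 30 was computed. At 28.0 to 28.8 evaluable, power is 80.1-81.2% by normal approximation and 78.7-79.9% by t-test. The worst of these is 1.3 points below target.
- *That the arms are 2 to 3 patients short of the requirement.* That is the gap in randomised patients (42 to 43 against 40). The evaluable shortfall is 1 to 2.
- *That an unstated 25% attrition rate was used*, since 30/0.75 = 40. The stated rates reach 40 by multiplication, so no hidden rate is needed.

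**Conclusion.** The point holds as an error in the inflation step. The stated 30, 10%, 20% and 40 do not fit together: 40 per group leaves 28.0 to 28.8 evaluable, 1 to 2 per arm below 30, and keeping 30 takes 42 to 43 per group (84 to 86 in total). Multiplication instead of division explains the printed figure. This is an inference from the match, since the section does not show its calculation.

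The effect on power is small, a drop from 81.5% to about 79-80% by t-test, or from 82.8% to about 80-81% by normal approximation. The trial stays at about its 80% target. This rests on the plan's own difference and SD, on reading the two losses as separate, and on both applying by the one-year comparison. It is a worthwhile correction of a stated figure and gives no reason to doubt the design.

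**What to change.** Keep 80 patients and replace the closing statement of the Sample size calculation section with wording such as: *Forty per group leaves 28 to 29 evaluable patients under 10% mortality and 20% loss to follow-up, giving about 79-80% power (t-test) for a 9-point difference with SD 12.* If the 20% was meant to include deaths, say so and give the corresponding figures: 32 evaluable per group and about 84% power.

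The cost is one sentence and a slightly less favourable stated figure; no patients are added. Should the sponsor prefer to guarantee 30 evaluable per group, the number to state is 42 to 43 per group, which adds 4 to 6 patients in total for a gain of about 2 to 3 percentage points of power. The power figures do not require this.

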### Statistical analysis

The research data will be reported following the CONsolidated Standards of Reporting Trial (CONSORT). Data will be analyzed using the Statistical Package for the Social Sciences (SPSS) version 16.0 or higher (SPSS, Chicago, Ill., USA). Normality of continuous data will be tested with the Shapiro Wilk test, and homogeneity of variances will be tested using the Levene's test. Protocol violations will be recorded; data will be analyzed with and without patients with protocol violation.

Differences in baseline characteristics (i.e., intrinsic and injury-related variables) between both intervention groups will be assessed using the Student's T-test (parametric numeric data), Mann-Whitney U-test (non-parametric numeric data) or Chi-square test (categorical data). Data will be presented as mean ± SD (parametric data) or medians and percentiles (non-parametric data).

Univariate analysis will be performed to test the difference in primary and secondary outcome measures between the intervention groups using the Student's T-test (parametric data), Mann Whitney U-test (non-parametric data) or Chi-square analysis (categorical data).

Multinomial logistic regression analysis will be performed to model the relation between different covariates and the Constant score. Intrinsic and fracture-related variables that display a p-value < 0.5 in univariate analyses will be added as covariate. Similar models will be made to model the relation between covariates and the other outcome measures.

A p-value < 0.05 (2-sided tests) will be taken as threshold of statistical significance.

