## Abstract

**Background:**

Fractures of the proximal humerus are associated with a profound temporary and sometimes permanent, impairment of function and quality of life. The treatment of comminuted fractures of the proximal humerus like selected three-or four-part fractures and split fractures of the humeral head is a demanding and unresolved problem, especially in the elderly. Locking plates appear to offer improved fixation; however, screw cut-out rates ranges due to fracture collapse are high. As this may lead to higher rates of revision surgery, it may be preferable to treat comminuted fractures in the elderly primarily with a prosthesis or non-operatively. Results from case series and a small-sample randomized controlled trial (RCT) suggest improved function and less pain after primary hemiarthroplasty (HA); however these studies had some limitations and a RCT is needed. The primary aim of this study is to compare the Constant scores (reflecting functional outcome and pain) at one year after primary HA versus non-operative treatment in elderly patients who sustained a comminuted proximal humeral fracture. Secondary aims include effects on functional outcome, pain, complications, quality of life, and cost-effectiveness.

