**Figure 4 F4:**
[figure not shown]
**Schedule of follow-up measurements**.

Clinical assessments will occur at the time of admission to the hospital (baseline), one week (3-10 days window), three weeks (11-28 days window), six weeks (4-8 weeks window), three months weeks (11-15 weeks window), six months (5-7 months window), 12 months (11-13 months window), and 24 months (24-26 months window) after surgery (HA group) or after start of conservative treatment (conservative group).

At baseline, multiple intrinsic (i.e., patient-related) and injury-related variables will be collected. At the three, six, 12, and 24 months FU visit, an independent researcher will determine the Constant score. In order to prevent bias the Constant score will be determined by an independent assessor. At each clinic FU visit, the researcher will ascertain patient status (i.e., secondary interventions, adverse events/complications, deaths), and will verify information within medical records. At each visit, patients will be asked to complete the questionnaires relating to disability (DASH score), and VAS for pain. From six weeks onwards, SF-36, EQ-5D, and health care consumption questionnaires will also be completed. A postal version of the latter questionnaire will be sent at 18 months in order to minimize recall bias.

As part of standard of care, X-rays of the shoulder will be made at the time of admission to hospital (baseline), at one, three and six weeks, and three and 12 months after surgery (HA group) or start of conservative treatment. CT scans that will be conducted pre-treatment, which are required for correct classification of the fracture, are also part of standard of care. As part of this trial, one additional CT-scan will be made at 12 months FU in order to determine consolidation (i.e. vanishing tubercles).

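### The one-year Constant score comparison has no effect measure fixed in advance, and the named tests leave the 3- and 6-month scores unused although 28–30% loss is expected

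*Protocol article*

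**What the plan says.** The primary endpoint is clear. The Abstract states: "The primary aim of this study is to compare the Constant scores (reflecting functional outcome and pain) at one year".

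The Statistical analysis section gives the comparison: "Univariate analysis will be performed to test the difference in primary and secondary outcome measures between the intervention groups". Which test applies depends on how the data are classed; the section lists the options as "using the Student's T-test (parametric data), Mann Whitney U-test (non-parametric data) or Chi-square analysis (categorical data". It does not say in so many words how data are sorted into parametric and non-parametric. The only related rule on distribution is "Normality of continuous data will be tested with the Shapiro Wilk test".

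Under Follow up of patients the score is taken repeatedly: "At the three, six, 12, and 24 months FU visit, an independent researcher will determine the Constant score". No baseline Constant score is mentioned there, and no longitudinal analysis is named.

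The Sample size calculation assumes "the mean Constant score will be 47 in the conservatively treated patients and 56 in the HA group". It takes the standard deviation to be 12 in both arms, obtains 30 per group and then raises this to 40: "Anticipating a mortality rate of 10% in the first year due to a natural death rate in elderly patients", plus 20% loss to follow-up. The Abstract promises analysis by intention to treat. A multivariable model of the Constant score is also planned, as multinomial logistic regression.

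**The concern.** There are two problems with what the plan fixes.

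First, the trial is sized to detect a difference between means, but the data decide whether a difference between means is tested. If the normality check rejects, the primary test becomes a rank comparison, which gives no difference in Constant points to set against the planned 9. The quantity being estimated should not depend on a preliminary test of the same data.

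Second, a two-group test at 12 months gives no weight to a patient without a 12-month score, even if that patient was scored at 3 and 6 months. The plan expects more than a quarter of patients to have no 12-month score. If leaving is related to earlier function, and differently so in the two arms, the observed 12-month means no longer compare like with like. In an unblinded comparison of surgery with non-operative care, such a difference is possible. A test that omits these patients also fits poorly with the promised intention-to-treat analysis.

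**Working it through.** **Inputs from the protocol.** Means 47 and 56 (difference 9), SD 12, two-sided alpha 0.05, power 0.80, 30 evaluable and 40 randomised per group, 10% deaths, 20% loss, scores at 3, 6, 12 and 24 months.

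**1. The plan's own figure.** Normal approximation: n = 2 × (1.96 + 0.84)² × 12² / 9² = 27.9, i.e. 28 per group. The exact t-test needs 28.9, i.e. 29. Dividing by the Mann-Whitney relative efficiency under normality, 28.9 / 0.955 = 30.3. The stated 30 is reproduced to within two patients.

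**2. Expected loss.** Multiplicative: 1 − 0.9 × 0.8 = 0.28. Additive: 0.10 + 0.20 = 0.30. Of 40 per group, 28.8 or 28.0 remain. The step from 30 to 40 itself allows 1 − 30/40 = 25%. The inflation treats lost patients as adding nothing to the test.

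**3. Power if loss is unrelated to outcome.** With 28 to 28.8 per group the t-test has power 0.79–0.80. Mann-Whitney on normal data has about 0.77–0.78. The planned test is close to nominal.

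**4. The normality check.** Simulation at 30 per group with no true difference, using Mann-Whitney if Shapiro-Wilk rejects in either arm:

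| Data | Type I error | Mann-Whitney used |
|---|---|---|
| Normal | 0.050 | 9% of trials |
| Skewed (beta) | 0.056 | 57% of trials |

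The error rate barely moves. What changes is the quantity reported.

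**5. Unused 3- and 6-month scores.** The correlations and dropout mechanisms here are assumptions; the protocol gives neither. Simulation: 40 per arm, SD 12, true difference 9, 26–36% missing at 12 months. Dropout depends on earlier observed scores (log-odds 1 per SD) where it is not random. The planned comparison is the difference in observed 12-month means; the alternative is a likelihood estimate that also uses the 3- and 6-month scores.

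| Correlation between visits | Bias of observed-score difference: low scorers leave HA, random loss in controls | Bias: low scorers leave controls, high scorers leave HA | Variance ratio, loss at random |
|---|---|---|---|
| 0.5 | +1.42 | −3.16 | 1.05 |
| 0.7 | +2.28 | −4.50 | 1.16 |
| 0.8 | +2.43 | −5.13 | 1.22 |

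The likelihood estimate was biased by at most 0.13 points. The variance ratios correspond to reductions of 1 − 1/1.05 = 5%, 1 − 1/1.16 = 14% and 1 − 1/1.22 = 18%.

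**6. Independent check.** A second simulation (correlation 0.5 and 0.7, low scorers leaving HA only, true difference 0) gave a bias of +1.95 and +2.70 points for the observed-score difference. Its type I error was 0.085 and 0.135. With random loss and a true difference of 9, power was 0.79 and 0.78 for the t-test, against about 0.85 and 0.86 for the likelihood analysis.

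**The case against.** A reader might infer that the plan prescribes a completers-only analysis. It does not. No sentence says so, the Abstract states intention to treat, and the handling of missing scores may sit in an analysis plan that is not shown. Its absence from the article is therefore not the fault raised here. What stands is narrower: the tests that are named use only observed 12-month scores, and the inflation from 30 to 40 is consistent with that.

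A single declared one-year endpoint with a two-group test is conventional and matches the sample size, and the normality check hardly affects the error rate. Both statements are right. Neither fixes the effect measure in advance.

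The size of the bias depends on assumed dropout patterns, and the model's near-zero bias follows from letting dropout depend only on observed scores. This is a fair limit. When 10 of the 30 percentage points of loss were placed before month 3 and tied to the unseen 3-month score, the model was itself biased by +0.5 to +0.9 or −1.1 to −1.8 points. It still did better than the observed-score comparison.

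About a third of the expected loss is death, which is not an ordinary missing score and which a mixed model does not resolve. This also stands.

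The planned multivariable analysis does not fill the gap. Multinomial logistic regression yields no mean difference in Constant points, and nothing says that it uses earlier visits.

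A reader might also infer that rank-testing costs would leave no mean cost difference for the cost-utility ratio. The protocol does not support that: under Outcome measures the ratio is separately defined from the difference in mean costs.

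**Conclusion.** The point holds in a limited form. The text supports two conclusions. The effect measure for the primary comparison is left to the trial data although the design rests on a mean difference of 9. The named tests also make no use of the 3- and 6-month scores despite 28–30% expected loss.

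The cost under random loss is modest: no bias, near-nominal power, and a forgone variance reduction of about 5–18% if visits correlate at 0.5–0.8. Under assumed arm-specific dropout related to earlier scores, the bias is roughly 1.4 to 5 points and its direction depends on who leaves. Against a planned difference of 9, the upper end is more than half the effect. These figures show what could happen; they are not forecasts for this trial. This is an improvement that should be made, not a flaw that invalidates the design.

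**What to change.** Name one primary analysis: a linear mixed model for repeated measures of the Constant score at 3, 6, 12 and 24 months, with treatment, visit, treatment-by-visit and an unstructured covariance. Include all randomised patients with at least one post-treatment score, in the arm to which they were allocated. The 12-month mean difference with its 95% CI is the primary estimate, whatever Shapiro-Wilk shows. Keep Mann-Whitney as a sensitivity analysis only.

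Report deaths separately from loss to follow-up. Add a missing-not-at-random sensitivity analysis that also covers patients lost before 3 months.

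The cost is a change of wording and slightly more analysis, with no new patients, visits or data. The model can be fitted in SPSS, the package already named. The downside is that the model assumes scores are missing at random given those observed, and it cannot recover patients with no score. That is still a weaker assumption than comparing observed 12-month scores alone requires.

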### Outcome measures

The primary outcome measure will be the Constant score. This scoring system consists of four variables, reflecting both function and pain of the shoulder joint [22]. The subjective variables are pain (15 points), activities of daily living (ADL; i.e., sleep, work, recreation/sport; 10 points), and arm positioning (10 points), which give a total of 35 points. The objective variables are range of motion (ROM; 40 points) and strength (25 points), which give a total of 65 points. ROM includes forward flexion (10 points), lateral elevation (10 points), external rotation related to the head (10 points) and internal rotation related to the spine column (10 points). Forward flexion and lateral elevation are measured using a goniometer. Strength of abduction will be measured using a calibrated spring balance. The right and left shoulders will be assessed separately.

Secondary outcome measures are:

- Disabilities of the Arm, Shoulder and Hand (DASH) score

- Visual Analogue Scale (VAS) for pain

- Rates of secondary interventions

- Radiographic healing

- Mortality rate

- Complication rates

- Health-related quality of life: Short Form-36 (SF-36)

- Health Utility: EuroQol-5D (EQ-5D)

- Healthcare consumption (for cost calculations)

- Cost-effectiveness

The Disabilities of the Arm, Shoulder and Hand (DASH) Outcome Measure is a validated 30-item, self-report questionnaire designed to help describe the disability experienced by people with upper-limb disorders and also to monitor changes in symptoms and function over time [23-25]. The DASH outcome measure is scored in two components: the disability/symptom section (30 items, scored 1-5) and the optional high performance Sport/Music module (4 items, scored 1-5). The DASH disability/symptom score is a summation of the responses to 30 questions on a scale of 1 to 5. Scores may range from 0 points (no disability) to 100 points (severe disability). The questions test the degree of difficulty in performing a variety of physical activities because of arm, shoulder, or hand problems (21 items). They also investigate the severity of pain, activity-related pain, tingling, weakness, and stiffness (5 items), as well as the effect of the upper limb problem on social activities, work, sleep, and self-image (4 items).

Pain level will be determined using a 10-point Visual Analog Scale, in which 0 implies no pain and 10 implies the worst imaginable pain.

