The EuroQol (EQ-5D) is a validated and extensively used general health questionnaire to measure quality of life [27,28]. It is recommended for the assessment of QoL in trauma patients, especially for economic assessments [29,30]. EQ-5D has been developed by the EuroQoL Group in order to provide a simple, generic measure of health for clinical and economic appraisal [31]. EQ-5D consists of the EQ-5D descriptive system and the EQ Visual Analog Scale (EQ VAS). The EQ-5D descriptive system comprises five dimensions: mobility, self-care, usual activities, pain/discomfort, and anxiety/depression. Each dimension is marked as either no problems, some problems, or severe problems, which results in a 1-digit number expressing the level selected for that dimension. The digits for five dimensions are combined in a 5-digit number describing the respondent's health state. The EQ VAS records the respondent's self-rated health on a vertical, visual analog scale. Scores ranging from 0 ('Worst imaginable health state') to 10 ('Best imaginable health state') can be used as a quantitative measure of health outcome as judged by the individual respondents.

Cost measurement will be in accordance with Dutch guidelines for economic evaluations. Healthcare consumption data will be collected using a custom-made questionnaire. Health care costs will include costs of general practice care, medical specialist care, physical therapy, hospitalization, medication, home care, and other costs directly associated with diagnosis, treatment and rehabilitation. Where possible standard cost prices will be used as published by Oostenbrink will be used [32]. In accordance with guidelines for differential discounting, effects will be discounted at a rate of 1.5% and costs at 4% per year [33]. Results will be presented with 95% confidence intervals.

The incremental cost-effectiveness ratio of HA versus conservative treatment will be expressed in a cost-utility ratio, i.e., in terms of cost per Quality-Adjusted Life Years (QALY). Cost-utility ratios will be calculated by dividing the difference in mean costs of the two interventions by the difference in their mean effects. Policy makers and healthcare economists have proposed that costs varying from € 25,000 up to € 75,000 (US$ 31,600 - US$ 94,700) per QALY may be considered as acceptable [34,35].

In addition to the outcome variables mentioned above, the following data will be collected:

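### The normality-driven test rule makes no exception for costs, so skewed costs would get a Mann-Whitney p-value that does not test the mean cost difference used in the cost-utility ratio

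*Protocol article*

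**What the plan says.** All references are to the protocol article.

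- **Statistical analysis, choice of test.** "Normality of continuous data will be tested with the Shapiro Wilk test". The plan will then "test the difference in primary and secondary outcome measures between the intervention groups using the Student's T-test (parametric data), Mann Whitney U-test (non-parametric data", with chi-square for categorical data. No secondary outcome is exempted.
- **Outcome measures, list of secondary outcomes.** The list contains "Healthcare consumption (for cost calculations", "Health Utility: EuroQol-5D (EQ-5D" and cost-effectiveness. QALYs are not listed by name.
- **Outcome measures, economic paragraphs.** "Cost-utility ratios will be calculated by dividing the difference in mean costs of the two interventions by the difference in their mean effects". The ratio is expressed "in terms of cost per Quality-Adjusted Life Years (QALY". Economic results are to carry 95% confidence intervals; the method is not named.
- **Statistical analysis, presentation.** "Data will be presented as mean ± SD (parametric data) or medians and percentiles (non-parametric data". This sentence closes the paragraph on baseline characteristics.

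Nothing says whether the economic paragraphs take precedence over the general test rule when costs are compared.

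**The concern.** Two instructions apply to the same cost data and aim at different quantities. The general rule leads, for skewed data, to a rank test, which asks whether a patient in one arm tends to cost more than a patient in the other. The economic evaluation asks whether the average patient costs more. For a budget or a cost-per-QALY ratio the mean is the relevant quantity whatever the distribution, because the few expensive patients are part of the bill.

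The difference bears on this trial's own hypothesis. Study objectives and Discussion expect higher initial costs with hemiarthroplasty (HA) but still expect it to be cost-effective, helped by lower later consumption. The secondary interventions listed for the conservative group only include arthroplasty and plate fixation. A plausible pattern is therefore a high, fairly uniform cost in the HA arm and a low typical cost with an expensive tail in the conservative arm. A rank test gives that tail little weight. The report could then carry a significant p-value for HA being dearer beside a ratio built on mean costs that are equal or point the other way.

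**Working it through.** **1. The plan's own figure.** The document gives no cost figures to reproduce. The sample size only sets the number of patients for the illustration. With a difference of 9, SD 12, two-sided alpha 0.05 and 80% power, n = 2 × (1.96 + 0.84)² × (12/9)² ≈ 28 per group (29 with the t distribution), against 30 stated. From 40 randomised per group, 10% mortality and 20% loss leave 40 × 0.90 × 0.80 = 28.8, about 29. I used 29 and 40 per arm, and 30 and 40 in step 4. The concern does not rest on this calculation.

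**2. Illustration A: index cost plus a re-operation cost. All prices and rates are assumptions.**
- HA: log-normal cost, mean EUR 11,000, SD 3,000; 5% of patients cost a further EUR 15,000. True mean = 11,000 + 0.05 × 15,000 = 11,750.
- Conservative: log-normal cost, mean EUR 5,000, SD 2,500; a share p is re-operated at a further cost c. True mean = 5,000 + p × c.

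| p, c | Conservative mean | True mean difference, HA − conservative | Median difference (approx.) |
|---|---|---|---|
| 27%, 25,000 | 11,750 | 0 | 5,000 |
| 20%, 25,000 | 10,000 | 1,750 | 5,500 |
| 10%, 20,000 | 7,000 | 4,750 | 6,000 |

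**3. Results of Illustration A (3,000 to 4,000 simulated trials per scenario).** Shapiro-Wilk rejects normality in the conservative arm in 98% to 100% of trials, so the rule selects Mann-Whitney.

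| p | n per arm | Mann-Whitney significant | Welch test of means significant | Mann-Whitney significant for HA dearer while the sample mean says HA cheaper |
|---|---|---|---|---|
| 27% | 29 | 71% | 5% to 7% | about 20% |
| 27% | 40 | 83% | 5% to 7% | 31% to 33% |
| 20% | 29 | 91% to 93% | 17% | about 12% |
| 10% | 29 | 99.9% | 85% | 0.1% |

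The 71% is not a false-positive rate of Mann-Whitney: the two distributions do differ. It shows that the test answers a different question.

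**4. Illustration B: a different model, also assumed.** Log-normal costs, mean = median × exp(s²/2), where s is the SD on the log scale. Unequal skew: HA median 10,000, s = 0.3, mean = 10,000 × exp(0.045) = 10,460; conservative median 6,000, so the medians always differ by 4,000. 5,000 trials per scenario.

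| Conservative s | Conservative mean | True mean difference, HA − conservative | Conflict as in the last column above, 30 per arm | 40 per arm |
|---|---|---|---|---|
| 1.0 | 9,892 | +568 | 13% | 19% |
| 1.2 | 12,327 | −1,866 | 25% | 37% |
| 1.4 | 15,987 | −5,526 | 30% | 45% |

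Differences are taken from unrounded means. With the same s in both arms (0.5 or 0.8), the conflict occurs in 0.1% of trials or fewer.

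**5. What drives the result.** Both models agree: the conflict needs unequal skew. It grows with the conservative tail and is almost absent when re-operations are few or skew is similar.

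**The case against.** The strongest reply is that the economic evaluation has its own paragraphs, which already specify means and 95% confidence intervals, and a specific provision is naturally read as overriding a general one. On that reading the quantity set against the cost-per-QALY thresholds is sound. This stands: the ratio is correctly specified, and a reader should not infer that the cost-effectiveness result would be computed wrongly.

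Three other stronger readings also fail.
- **QALYs.** A reader might infer that QALYs are a listed secondary outcome and so fall under the rule directly. They are not listed; EQ-5D and cost-effectiveness are, and the rule reaches QALYs only by inference.
- **Medians.** A reader might infer that the plan requires "medians and percentiles (non-parametric data" for costs. That sentence stands in the baseline paragraph. The outcome paragraph names tests and no summary statistic.
- **Opposite conclusions.** A reader might infer that two tests will contradict each other. In Illustration A at 29 per arm, significant Mann-Whitney and Welch results in opposite directions occurred in 0% of trials, and the true mean difference is never reversed. The conflict there is between a significant rank test and the direction of the sample means.

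It can also be said that the listed item is resource use rather than total cost, and that cost-effectiveness is an arm-level ratio to which neither test applies, so the test sentence was perhaps not written with economics in mind. That is likely, but the listed item is tied to costs and the sentence covers secondary outcomes without exception. Finally, bootstrap details may be left to a fuller plan, and their absence is not the point. The point is a stated rule that, taken as written, selects a test of the wrong quantity for cost.

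**Conclusion.** The concern holds in a limited form. As written, the test rule covers the cost outcome, would select Mann-Whitney for skewed costs, and so yields a p-value that does not address the difference in means on which the ratio is built. Whether the two visibly disagree depends on unequal skew between arms. Under the assumed inputs, the significant rank result and the sample mean difference point in opposite directions in 0% to 45% of trials, and essentially never with equal skew or 10% re-operated. No price or re-operation rate is in the document, so this range shows sensitivity to assumptions and does not predict the trial. A named secondary aim is affected; the primary outcome and sample size are not. Clarification is worthwhile because the conflict is in the stated text and is cheap to remove.

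**What to change.** Add one sentence to Statistical analysis. Costs and QALYs are exempt from the normality-driven choice of test and follow the economic paragraphs under Outcome measures: the arithmetic mean per arm and the difference in means with a 95% confidence interval, whatever the distribution. A non-parametric bootstrap that resamples patients, keeping each patient's cost and QALY together, is one suitable method. Medians may be shown as description only.

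This needs a short bootstrap program and no new data, visits or patients. The downside is that the cost comparison is less likely to reach significance: in Illustration A with 20% re-operated and 29 per arm, a test of means is significant in 17% of trials, against 91% to 93% for Mann-Whitney. The lower figure reflects the real uncertainty about mean cost.
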